## Abstract

*Background and objectives*: Available evidence shows a low uptake of HIV services among men in Rwanda. HIV self-testing (HIVST), a new intervention, may have the potential to improve the uptake of HIV testing services among men. The current study aims to adapt a health education program (HEP) for improving the uptake of HIVST among men in Rwanda. *Materials and Methods*: We propose a mixed method study, which will be conducted in four phases. In Phase 1, we will conduct a scoping review to map the available evidence on health education programs for men in low- and middle-income countries (LMICs). In Phase 2, we will conduct interviews with stakeholders in the Rwanda HIV response and healthcare providers to determine their perspectives on implementation of HIVST in Rwanda. In Phase 3, a cross-sectional survey will be used to assess HIVST awareness and acceptability among men in Rwanda. Guided by findings from Phases 1, 2, and 3, we will employ the nominal group technique to develop and optimize the HEP for improving the uptake of HIVST among men in Rwanda. In Phase 4, we will use a pragmatic pilot randomized controlled trial to assess the preliminary impact of the HEP for men in Rwanda and assess the feasibility of a later, larger study. We will employ the Stata version 16 statistical package and NVivo version 12 for the analysis of quantitative and qualitative data, respectively. We anticipate that the findings of this study will inform implementers and policy makers to guide strategies on the implementation of HIVST in Rwanda and ultimately accomplish goals set forth in the Rwanda 2019–2024 Fourth Health Sector Strategic Plan on scaling up the number of men who know their HIV status. *Conclusion:* It is anticipated that this study will proffer solutions and strategies that are applicable not only in Rwanda but also in similar settings of LMICs.

## Contributions to the Literature

-Policy development for the implementation of HIV self-testing varies from country to country, indicating that the implementation strategies would differ accordingly.-The current study will utilize a pragmatic approach to adapt and optimize a health education program that may be applicable to the local context but also proffer solutions for similar low- to middle-income country (LMIC) settings.-Currently, there is a paucity of evidence on health education programs (HEPs) targeted for men specifically for HIV self-testing uptake.

## 1. Background

Human immunodeficiency virus (HIV) currently remains a major public health problem in Rwanda. In 2014, the Joint United Nations Programme on HIV/AIDS (UNAIDS) and partners launched the 90-90-90 targets for 2020 that call for 90% of people with HIV to be diagnosed, 90% of the diagnosed to access ART, and 90% of the treated to be virally suppressed [1]. Worldwide, different interventions that aim to scale up HIV diagnosis, antiretroviral therapy (ART) initiation, and care continuum have led to most countries nearing epidemic control [2,3]. However, available evidence shows a low uptake of HIV testing services (HTSs) among men [4]. 

The first documented AIDS cases in Rwanda were in 1983 [5]. Rwanda has the 18th highest HIV prevalence in the world [3]. Since 2005, HIV prevalence in Rwanda has been constant at around 3% [6]. Specifically for the age group 15–49, HIV prevalence in Rwanda has disparities by sex, with 4% and 2% among women and men, respectively [6]. As of 2017, UNAIDS reported Rwanda to be nearing epidemic control for HIV with a steady decrease in HIV incidence (from 12,500 new cases in 2007 to 5000 in 2017) and AIDS deaths (from 12,500 in 2007 to 10,000 in 2017) [3,7,8,9]. A low uptake of HTSs remains a public health priority in Rwanda [6]. Findings from a recently concluded population-based HIV impact assessment study revealed that only 80.4% of HIV-positive men knew their HIV status [10]. This was much lower to their women counterparts; 85.6% of HIV-positive women knew their HIV status [10]. This underscores the need to improve the first 90 among men. In response to this, one of the strategies highlighted in the Rwanda Ministry of Health 2019–2024 Fourth Health Sector Strategic Plan is the scaling-up of male-targeted interventions with the main focus on increasing the uptake of HTSs [11]. 

Epidemic control of HIV infection depends on the success of the strategies to prevent new infections and increase the treatment availability and uptake for currently infected individuals [2,12]. For prevention and treatment interventions, the importance of knowing one’s HIV status cannot be over-emphasized. While this is the case, men (ranging between 51% and 70%) lag behind women (ranging between 71% and 84%) on the uptake of HTSs, a gap threatening the progress towards the 90-90-90 goals [3,4,13]. A poor uptake of HTSs among men has been attributed to patriarchy and masculinity [14,15]. These sociocultural factors refer to the socially determined stereotypes, which are infringed on men as acceptable “manliness”. These cultural and traditional masculine identities have been constructed by the societies and often inform men’s health seeking behavior [14]. Poor service delivery, long waiting times to obtain the results, concerns over confidentiality, and HIV related-stigma have been reported elsewhere as impeding men’s uptake of HTSs [13,15,16]. The World Health Organization (WHO) published the first global guidelines on HIV self-testing (HIVST) in 2016 [17]—an intervention that has shown global potential to increase uptake of HTSs [13,18,19,20,21]. Studies have reported success, with HIVST being offered to men in health care facility-based settings [22,23] and community settings [22], in Malawi, Zambia, and Zimbabwe. An HIVST scale-up study conducted in these three African countries revealed promising results. A higher proportion of male self-testers (22.3%), compared with women (17.1%), were first-time testers, which was apparent in Zimbabwe (16.2% vs. 11.4%), Zambia (25.4 vs. 17.7%), and Malawi (27.9 vs. 25.9%) [22]. Several other different scholars have shown HIVST as an acceptable strategy to improve men’s uptake of HTSs [16,24,25,26]. In the Rwandan context, HIVST may have potential to address men’s barriers of HTSs associated with facility-based testing [24,27,28]. In Rwanda, a lack of awareness on HIVST has been revealed as an important barrier to uptake [28]. 

Historically, health education programs (HEPs) have been shown to play an important role in not only the provision of knowledge to individuals concerning their health but also building skills and changing attitudes regarding health issues [29]. Given that the factors that contribute to male aversion to HTSs are multifaceted, they require equally complex interventions [30]. The primary aim of this study will be an adaptation of an HEP for improving the uptake of HIVST by men in Rwanda. It is anticipated that the results of this will proffer solutions and strategies that are applicable for men in similar settings of low- to middle-income countries (LMICs).

### 1.1. Ethical Considerations

This study has been ethically reviewed and approved by four institutional review boards: The Rwanda National Ethics Committee (Approval number: 332/RNEC/201), the University Teaching Hospital of Kigali Ethics Committee (Approval number: EC/CHUK/0111/2019), Rwanda Military Hospital Institutional Review Board (Approval number: RMH IRB/036/2019) and the University of KwaZulu Natal Biomedical Research Ethics Committee (Approval number: BE/280/19). All participants will sign a consent form (Additional File) prior to participation in the study.

### 1.2. Trial Registration

Pan African Clinical Trial Registry, PACTR201908758321490), Registered 8 August 2019, https://pactr.samrc.ac.za/TrialDisplay.aspx?TrialID=8310.

## 2. Methods

### 2.1. Study Design

Guided by the Standard Protocol Items: Recommendations for Interventional Trials (SPIRIT), we propose a multi-phase mixed method study. In Phase 1, we will conduct a scoping review to map available evidence on HEPs for men in LMICs. We chose to use the scoping methodology, a useful approach for determining the need for, and value of, a full systematic review. In Phase 2, we will conduct interviews with stakeholders in the Rwanda HIV response and healthcare providers to determine their perspectives on the implementation of HIVST in Rwanda. In Phase 3, a cross-sectional survey will be used to assess HIVST awareness among men in Rwanda.

Guided by findings from Phases 1, 2, and 3, we will employ the nominal group technique [31] to co-create and optimize the HEP for improving the uptake of HIVST among men in Rwanda. In Phase 4, we will use a pragmatic pilot randomized controlled trial (RCT) to assess the feasibility of a larger trial and the preliminary impact of the HEP.

### 2.2. Theoretical Framework

Two models will guide this study. The Consolidated Framework for Implementation Research (CFIR) [32] and the Theory of Change (ToC) [33]. The CFIR will frame the overall project design across methods. This framework was adapted to suit the study. The CFIR provides a menu of constructs that can be used in a range of applications [32]. The domains of the framework include intervention characteristics, an inner setting, an outer setting, the characteristics of individuals involved in the implementation, and the implementation process [32]. All these domains affect an intervention’s implementation. The process flow for development and optimization of HEPs will be guided by the CFIR. To adapt and optimize the HEP, a co-creation workshop will be done. A literature review by Greenhalgh et al. [34] revealed co-creation models to be an increasingly popular approach to aligning research and service development with the potential to deliver significant societal impact via dynamic, locally adaptive community-expert partnerships. A co-creation workshop of the community-based participatory research model [35] will be employed. This model has been shown to be useful when power imbalances between researchers and community members exist [35]. 

This study will be guided by the theory of change (ToC) [33]. The theory of change is a useful methodology for planning, participation, and evaluation applied to initiatives that are implemented to drive social change [36]. The main domains for a ToC are the inputs, outputs, outcomes, and impact [33,36,37]. Although ToCs come in different variations, there are key components that remain the same in each model. They begin with the determination of a final outcome and then map backwards from this goal towards the conditions needed to reach this goal [37]. A ToC is most useful in the areas of monitoring and evaluations of programs designed for significant social impact [38]; however, under this umbrella could be many other designated areas that include policy making [33]. Specifically, for the purposes of this study, the ToC will drive the individual-level HIVST intervention to be piloted in Phase 4. 

### 2.3. Study Setting

Kigali City Province is the capital city of Rwanda. There are three districts, namely Gasabo, Kicukiro, and Nyarugenge, 35 sectors, 161 cells, and 1183 villages in Kigali [39]. The population of Kigali was 1,132,686, with an estimated urban population of 859,332, as of 2012 [39]. At this time, the majority of the residents were male (51.7%) [39]. There are a total of 42 health facilities in Kigali; 21 in Gasabo, 10 in Kicukiro, and 11 in Nyarugenge [39]. HIV prevalence in Kigali has disparities by sex, with 8.0% among women and 4.4% among men. However, at the national level, HIV prevalence is 3.6% and 2.2% among women and men, respectively [6]. Among men across the three districts, HIV prevalence was reported to be 6.0% in Nyarugenge, 4.9% in Kicukiro, and 4.4% in Gasabo [6].

### 2.4. Phase 1: Scoping Review 

Objective 1: To conduct a scoping review on HEPs for men’s engagement in health services in LMICs.

Design: The scoping review protocol has been developed a priori and has been published elsewhere [40]. The scoping review will be reported according to the PRISMA Extension for Scoping Reviews (PRISMA-ScR) guidelines [41]. 

Data Source: Eligible studies will be selected guided by an inclusion and exclusion criteria. 

Analysis: We will use NVivo version 12 to extract relevant outcomes and thematic analysis of the studies.

Outcome Measures: A narrative report of evidence on HEPs for men’s engagement in health services in LMICs. 

### 2.5. Phase 2: Qualitative Study

Objective 2: To determine key stakeholders’ perceptions on the implementation of HIVST in Rwanda.

Design: A qualitative study design will be employed [42]. We will purposively sample and enroll a minimum of eight key stakeholders based on the researcher’s judgment that they would contribute valuable insights on HIVST implementation in Rwanda. An interview guide will be used to guide the discussion (Supplementary File 1). The interview guide will probe for information on the current status of HIVST implementation in Rwanda, the perceived challenges, and strategies for implementation and scale-up. All interviews will be tape-recorded. We will transcribe verbatim all tape-recorded interviews. Where applicable, the transcribed text from each respondent will be translated from Kinyarwanda, the local language, to English.

Data Source: Data will be gathered through in depth-interviews.

Analysis: Thematic content analysis will be based on the naturalistic paradigm [43] following the hybrid approach [44].

Outcome measures: A narrative report of key stakeholder and health care providers perspectives on the implementation of HIVST in Rwanda. Perspectives will be assessed using the intervention characteristics domains of the CFIR (Table 1).

### 2.6. Phase 3: Cross Sectional Survey

#### 2.6.1. Objective 3: To assess HIVST Awareness among Men in Kigali, Rwanda

Design: A cross-sectional study will be employed. One health facility will be selected in each district. Due to the nature of the study design, and assuming that the population is >10,000 and that there is an unknown level of awareness of HIVST among men in Rwanda, the overall sample size will be deduced using the formula below:
(1)$$n=\frac{Z^{2}\times \;\mathrm{pq}\;}{d^{2}}$$
(2)$$n=\frac{1.96^{2}\times \left(0.5\right)\times \left(1-0.5\right)}{0.05^{2}}$$
where *n* = 384 participants.

For HIVST acceptability, assuming the acceptability rate of 94% reported in Kenya [45], the calculated sample size based on the formula above is 241 participants. For the purposes of this study, the desired sample size will be the highest of the two outcome variables. Sample size will not be adjusted for design effect as we will purposively select one tertiary facility in each district hence limiting the issue of error commitment during the recruitment. To determine the minimum sample size per facility, the probability proportionate to size will be used. A sampling frame for each study site will be developed based on the number of the out-patient departments’ male clinic attendees. Table 2 illustrates how sample size will be calculated for each study site and sampling strategy. Enrollment of participants will be by systematic random sampling. All men visiting the facility for the following reasons will be eligible to participate for the study (accompanying someone, visiting someone, or seeking health services). Healthcare workers will be excluded as they are considered implementers of HIVST thus expected to be knowledgeable on the intervention.

Data collection will be conducted using a self-administered semi-structured questionnaire (Supplementary File 2). The questionnaire will address demographic characteristics, health status and sexual behavior, health seeking behavior, and knowledge, attitudes, and perceptions (KAPs) toward HIVST.

Data Source: A semi-structured questionnaire will be employed.

Analysis: Quantitative variables will be summarized by means and standard deviation. Qualitative variables will be summarized using frequency distribution. We will use the student t-test or the chi-square test to determine study variables associated with age awareness and the acceptability of HIVST. Univariate binary logistic regression analysis will be carried out to obtain preliminary insight into the unconditional association of each independent variable and dependent variables (awareness and acceptability). Multiple logistic regression will be employed to determine explanatory variables associated with awareness or acceptability status while adjusting for other study variables. All statistical tests will be concluded at a 5% level of significance employing Stata version 16 statistical package.

Outcome measures: We will assess two outcome measures: awareness and acceptability. Awareness will be considered as a yes response to the question “Do you know what HIVST is?”. Acceptability will be assessed by the question “As of 20 February 2017, it is recommended by the MOH to use HIVST kits as an additional strategy to reach out to people who are not yet tested, and there are plans for a national roll-out. Do you agree with this recommendation?”

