**Phase 3: Objective 3 To assess HIVST awareness among men in Rwanda**			
Awareness	N/A	Demographic characteristics, knowledge, attitudes, HIV risk perception, and health seeking behavior characteristics	Descriptive statistics or estimates based on 95% confidence intervals (CI) Logistic regression
Acceptability			

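### Phase 3 survey: purposive choice of facilities is not a valid reason to omit a design effect, and 384 men give ±5 points only for men visiting the three chosen facilities

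*Protocol article*

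**What the plan says.** Section 2.6.1 of the protocol article sizes the survey for an unknown level of awareness, with Z = 1.96, p = 0.5 and d = 0.05, and arrives at "384 participants". This is the larger of the sample sizes for awareness and acceptability, so it governs. On clustering the section says "Sample size will not be adjusted for design effect as we will purposively select one tertiary facility in each district", and it gives the benefit as "hence limiting the issue of error commitment during the recruitment". Within each facility, men are enrolled by systematic random sampling. Probability proportionate to size is used to divide the 384 men among the three sites (Table 2), not to choose the sites.

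The target population is described in two ways. The heading of section 2.6.1 reads "To assess HIVST Awareness among Men in Kigali, Rwanda"; the Phase 3 row of Table 3 reads "To assess HIVST awareness among men in Rwanda". Section 2.1 also speaks of men in Rwanda.

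For the adjusted analysis, section 2.6.1 says: "Multiple logistic regression will be employed to determine explanatory variables associated with awareness or acceptability status while adjusting for other study variables". The Phase 3 factors listed in Table 3 are demographic characteristics, knowledge, attitudes, HIV risk perception and health-seeking behaviour. Facility is not among them.

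**The concern.** A design effect arises because men at the same facility tend to resemble one another. How the facility was picked does not change that. Purposive choice in fact weakens the route to a wider population, because the facilities then have no known selection probabilities. The stated reason therefore cannot support the decision it is given for.

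Two positions would be coherent. If the three facilities stand for a larger set, they are three clusters, and the simple-random-sample margin is too narrow. If they are fixed sites of interest, no design effect is needed, but inference stops at men who visit them. The article takes neither position: it uses the formula that fits the second and keeps target populations that belong to the first.

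At stake is how the awareness and acceptability estimates, and their associations with other variables, are read. Objective 4 uses them, with the scoping review and the stakeholder interviews, to shape the health education program.

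**Working it through.** **Inputs from the protocol article.** Z = 1.96, p = 0.5, d = 0.05 and n = 384 (section 2.6.1); three facilities, one per district (sections 2.3 and 2.6.1); site allocations of 170, 128 and 86 from monthly attendance of 400, 300 and 200 (Table 2, presented as an illustration); 42 health facilities in Kigali (section 2.3). No ICC is given.

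**1. The plan's own figure.** n = Z² × p × (1 − p) / d² = 1.96² × 0.25 / 0.05² = 384.16. The stated 384 is reproduced.

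**2. Facilities as fixed strata.** Weights proportional to attendance are 400/900, 300/900 and 200/900, that is 0.444, 0.333 and 0.222. With p = 0.5 at each site:

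Variance = 0.25 × (0.444²/170 + 0.333²/128 + 0.222²/86) = 0.25 × 0.002604 = 0.000651

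Half-width = 1.96 × √0.000651 = 0.0500, or ±5.0 points. So 384 men deliver the planned precision for men visiting these three facilities, with no inflation.

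**3. Illustration with facilities as a random draw.** Take m = 384/3 = 128 men per site, design effect DE = 1 + (m − 1) × ICC, and half-width = 1.96 × √(0.25 × DE / 384). The ICC values are assumptions.

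| Assumed ICC | DE | Effective n | Half-width |
|---|---|---|---|
| 0.001 | 1 + 127 × 0.001 = 1.13 | 341 | ±5.3 points |
| 0.01 | 1 + 127 × 0.01 = 2.27 | 169 | ±7.5 points |
| 0.05 | 1 + 127 × 0.05 = 7.35 | 52 | ±13.6 points |

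Using the unequal sites of Table 2 changes little. The size-weighted m is (170² + 128² + 86²)/384 = 137.2, which gives ±7.7 points at ICC 0.01 and ±14.0 at 0.05.

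**4. Whether more men would help.** With three facilities, the half-width cannot fall below 1.96 × √(0.25 × ICC / 3), however many men are enrolled. This floor reaches 5 points at ICC = 3 × (0.05/1.96)² / 0.25 = 0.0078. Above that value, more men at the same three sites would not reach ±5 points for a wider population. Nor would inflation address the purposive choice of sites or the restriction to men who visit a tertiary facility.

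**The case against.** The strongest reply is that the decision itself survives. With the facilities as fixed strata, 384 men and no design effect are correct, so only the sentence that explains the decision is wrong. That stands, and it is why the remedy is a narrower claim and not a larger sample.

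It can also be said that the article already shows who is sampled: the frame is built for each site from male out-patient attendees, and eligibility is limited to men visiting the facility. Table 3 states no ±5 points; it promises only descriptive statistics or estimates with 95% confidence intervals. This is fair. The article never says in so many words that ±5 points holds nationally. What remains is that the objective names Kigali in one place and Rwanda in another, and that no passage limits the inference to the three sites.

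The absence of a facility term is weaker evidence. The models adjust for other study variables, and an article may leave the full covariate list to a longer document. Facility is simply not named in Table 3, and nothing excludes it. Unadjusted univariate models suit their stated purpose and need not change, and a stratified test in place of the plain chi-square would be a preference.

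Finally, this is a formative survey. Table 3 gives it no success criterion, and no decision is tied to a ±5-point margin.

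A reader might infer from the illustration that the survey is undersized and needs a design effect of 2 to 7. The documents do not support that: they give no ICC, the site counts are illustrative, and the sites are not a random draw. A reader might also infer that associations will be confounded by facility. The documents contain no awareness or acceptability data by site, so this is only a possibility to guard against.

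**Conclusion.** The stated rationale is wrong, and the target population is wider than the design supports. Purposive selection of one facility per district does not remove between-facility variation and gives no design-based margin of error for men in Kigali or men in Rwanda. The 384 men give ±5.0 points for men visiting the three selected facilities. This rests on treating the facilities as fixed strata, on proportional allocation, and on p near 0.5.

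For any wider population the shortfall cannot be quantified from the documents. The range of ±5.3 to ±13.6 points depends on assumed ICCs of 0.001 to 0.05 and on treating the sites as randomly drawn, which they are not. It shows only that the gap could be negligible or large. The point does not touch the Phase 4 pilot randomized trial. Its weight is minor to moderate.

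**What to change.** - Delete the sentence that ties the absence of a design effect to purposive selection. Say instead that the three facilities are treated as fixed strata and that inference is limited to them.
- Define the Phase 3 target as men visiting the three selected facilities, and use that definition in the heading of section 2.6.1, the sample-size text and Table 3.
- Claim ±5 points only for that population.
- Report awareness and acceptability for each facility, and as stratified overall estimates, with 95% confidence intervals.
- Include facility indicators in the multiple logistic models. The univariate models may stay unadjusted.

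The cost is some rewording, two additional terms per multiple model and a narrower claim. No extra participants are needed. Keeping men in Kigali as the target would be a different design: more facilities, selected by a probability method, with a stated ICC and design effect.

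### The Phase 3 acceptability model rests on about 23 non-accepting men at the plan's own 94% rate, yet it is specified and tested exactly like the awareness model

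*Protocol article*

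**What the plan says.** Section 2.6.1 sizes the survey with a single-proportion precision formula. For awareness, with p = 0.5 and d = 0.05, the result is 384. The second outcome is introduced with "For HIVST acceptability, assuming the acceptability rate of 94% reported in Kenya", and 241 men are said to be needed. One sample then serves both: "the desired sample size will be the highest of the two outcome variables", which is 384.

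The Analysis paragraph of the same section gives both outcomes one model: "Multiple logistic regression will be employed to determine explanatory variables associated with awareness or acceptability status while adjusting for other study variables". A univariate logistic step comes first, described only as preliminary. All tests are at the 5% level. The Phase 3 row of Table 3 names logistic regression and gives awareness and acceptability the same candidate factors: "Demographic characteristics, knowledge, attitudes, HIV risk perception, and health seeking behavior characteristics". Neither place distinguishes the two outcomes.

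Section 2.6.2 lists the survey findings on awareness and acceptability among the inputs to the panel that develops the HEP.

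**The concern.** The information in a logistic model is governed by the rarer outcome class rather than by the total number of men. The sample size rule looks only at the precision of each proportion. By that measure acceptability is the less demanding outcome, so 384 appears more than enough for it. For the regression the order reverses: a proportion near 94% leaves few men in the smaller class, and acceptability becomes much the weaker of the two analyses.

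At stake is how the acceptability results are read. If the two models are presented on the same footing, a factor that is not significant for acceptability may be taken by the HEP panel as no barrier, when the survey had little chance of detecting it. An occasional infinite or inflated odds ratio could mislead in the other direction.

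**Working it through.** **Inputs from Section 2.6.1.** Z = 1.96; p = 0.5 and d = 0.05 for awareness; 94% acceptability; common N = 384; 5% tests (taken here as two-sided).

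**Assumed, not in the document.** The number of model coefficients, the prevalence of factor categories, and a true odds ratio of 2.

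**1. The plan's figure.** n = 1.96² x 0.5 x 0.5 / 0.05² = 384.16, which reproduces 384. (The 241 for acceptability needs d = 0.03, giving 240.7; d = 0.05 gives 86.7. This does not alter the chosen 384.)

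**2. Smaller outcome class.**
- Awareness: 384 x 0.50 = 192.
- Acceptability: 384 x 0.06 = 23.04. The 95% range of a binomial with n = 384 and p = 0.06 is 14 to 33.

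**3. Non-acceptors per coefficient.** One coefficient for each of the five factor groups in Table 3 gives 23.04/5 = 4.6. Ten give 2.3, fifteen 1.5 and twenty 1.2.

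**4. Precision.** In simulated surveys of 384 men with a 6% outcome and independent binary factors at 30% prevalence, the median standard error of one log odds ratio was 0.445 with 2 factors and 0.471 with 15. The ratio of upper to lower 95% limit is exp(2 x 1.96 x SE), so 5.7 and 6.3. For awareness, simulated ratios were 2.3 to 2.4 (true factor at 40% prevalence).

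**5. Bias.** With a true log odds ratio of 0.69, the simulated mean under ordinary maximum likelihood rose to about 0.72 to 0.81 as factors were added. As odds ratios that is exp(0.72) = 2.05 to exp(0.81) = 2.25, against 2.

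**6. Infinite estimates.** A coefficient is infinite if, for example, no non-acceptor falls in a factor category. For a null binary factor of prevalence π that chance is (1 − 0.06π)^384; for k independent factors the chance of at least one is 1 − [1 − (1 − 0.06π)^384]^k.

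| Prevalence of factors | Chance per factor | k = 10 | k = 20 |
|---|---|---|---|
| 40% | 0.00009 | 0.1% | 0.2% |
| 30% | 0.00093 | 0.9% | 1.9% |
| 20% | 0.0097 | 9% | 18% |
| 10% | 0.099 | 65% | 88% |
| spread evenly over 10 to 50% | 0.0107 (average) | 10% | 19% |

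Simulated rates agree closely: about 1 to 2% at 30% prevalence and 8 to 20% with prevalences of 10 to 50%, for 10 to 20 factors. A Firth-penalised fit with 15 factors removed the separation and most of the bias.

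**7. Power.** For one balanced binary factor with odds ratio 2 and 6% non-acceptance overall, the two rates are 0.0411 and 0.0789, with 192 men in each group. The pooled standard error is √(2 x 0.06 x 0.94/192) = 0.02424 and the unpooled one is 0.02416. Power = Φ[(0.0378 − 1.96 x 0.02424)/0.02416] = Φ(−0.40) = 0.34. Simulated power in adjusted models was 0.36, 0.37, 0.37 and 0.36 with 2, 10, 15 and 20 factors. For awareness it was 0.90 to 0.92.

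**8. False selection.** In the simulations a null factor was rejected in about 3 to 5% of surveys, so the 5% test is not inflated.

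**The case against.** The strongest reply is that this is a condensed article. A final covariate list and the handling of sparse cells are commonly left to a fuller document, and saying nothing about a cap is not a commitment to enter every variable. That is right as far as it goes: the absence of a list is not the point made here. What the article does state is the 94%, the common 384 and one ordinary adjusted model at 5% for both outcomes, and these fit together poorly for acceptability.

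A reader might infer that the sample simply cannot support an acceptability model, that overfitting explains the low power, and that factors would be selected by noise. The material does not support this. Power stays near 0.35 from 2 to 20 factors, so a shorter model would not restore it. Null factors are not selected too often. Bias is modest, and separation is rare unless some categories are uncommon.

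Two further points stand. The 94% is a Kenyan planning value; at 90% there would be 38 non-acceptors and at 80% there would be 77. The influence on the HEP is also indirect: the survey is one of three sources put to a panel, and no rule makes adjusted p-values decide the content.

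**Conclusion.** The point holds in a limited form. At the plan's own figures, the acceptability model has about 23 men in its smaller class against 192 for awareness, and it should not be specified and read in the same way. The main cost is imprecision, with confidence limits about sixfold apart. Added to that are modest bias and a separation rate that ranges from negligible to serious according to how rare the factor categories are. Low power for an odds ratio of 2 is a fact about a 6% outcome in 384 men and a reason to label the results exploratory; it is not evidence of overfitting.

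The 23 and the 192 follow from the document alone. The separation, bias and power figures rest on assumed factor counts, prevalences, independence of factors and effect size. The estimated proportions aware and accepting are unaffected, and the Phase 4 pilot uses different data. The change is worth making but is not critical.

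**What to change.** In the Analysis paragraph of Section 2.6.1 and the Phase 3 row of Table 3, treat the two outcomes separately.

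- **Awareness:** keep multiple logistic regression as written.
- **Acceptability:** state that about 23 non-accepting men are expected at 94%. Fit a Firth-penalised logistic model with a short factor list fixed in advance. Report the estimates as exploratory with 95% confidence intervals, and say that a non-significant factor is not evidence that no barrier exists when the HEP is developed.
- **Contingency:** allow the fuller model if observed non-acceptance proves much higher than 6%.

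This changes wording only and needs no more participants or data. The price is that fewer factors are adjusted for and determinants of acceptability carry an exploratory label. Penalisation deals with infinite estimates and most of the bias. It does not restore power, which is why the label and the intervals are part of the change.
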